#### **9.11. Definition of End of Study**

The end of study is the point at which all the study data has been entered and queries resolved.

### **10. SAFETY REPORTING**

Potential AEs will be recorded at pre-operative follow-up assessment 1 and the post-operative assessment. Participants may contact the research team (e.g., over the phone) at any time point during the course of the study to report potential AEs. AEs will be recorded as part of the eCRF of the subsequent assessment (e.g., an AE occurring between pre-operative assessment 1 and 2 will be recorded as part of the pre-operative assessment 2).

One previous trial reported no SAEs due to the TDR, whereas another reported two SAEs potentially related to the TDR in the same participant.[21, 22] There was evidence that for every five people one would experience an adverse, mostly mild, event because of the TDR programme.[21] Constipation, headache, fatigue, and dizziness are the most common AEs albeit occurring in a minority of participants (<8% each) and disappeared over time.[21, 22] Less common side effects include dry mouth, abdominal pain, bad breath, diarrhoea, hair loss, dry skin, mood changes, and feeling cold.

The safety reporting window begins from the first day of the intervention for participants in the intervention group and from the day of randomisation for participants in the control group. It finishes for both groups when the participant completes the study. The limit of investigator follow-up of SAEs will be until the participant completes the study. This requirement will be the same for all SAEs.

Operative and post-operative complications or the responses to questionnaires (e.g., change in anxiety levels) will not be reported as AEs, as they will be extracted as part of the study outcomes.

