|                 | 10. Adverse events                                                                                                                                                                                                                              | xxv. Healthcare resource use
xxvi. QALYs
xxvii. Adverse events                                                                                                                                                                                                                                                                                                                                                                                                                           | xxv-xxvi: Baseline, 30 days post-operatively

xxvii: Baseline, pre-operative assessment and 30 days post-operatively                                                                                                                                                                                                                                     |
| Process         | 
To examine the
 
 
Experience of the intervention
 
Experience of the trial
 
Control group contamination
 
Fidelity of delivery
 
Barriers to trial enrolment
 
 | 
 
Analysis of qualitative interviews with intervention participants
 
Feedback pre-operatively
 
Feedback post-operatively
 
Feedback post-operatively
 
Analysis of QuinteT qualitative interviews with participants and staff
 
Analysis of audio-recorded recruitment appointments
 
Feedback post-operatively
 
Observation of consultations
 
Reasons for declining participation
 
 | 
 
Pre-operative assessment 2
 
Pre-operative assessment 3
 
30-days post-operatively
 
30 days post-operatively
 
Pre-operative assessment 1 and throughout the trial
 
Screening
 
30 days post-operatively
 
Throughout the intervention
 
Screening
 
 |

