One in 5 people experience an adverse, mostly mild, event due to the intervention.[21] Constipation (1 in 7), fatigue (1 in 12), headache (1 in 17), and dizziness (1 in 22) are the most common Adverse events (AEs) albeit mild (only 11% were moderate or severe), reduce in intensity over time and disappear as soon as the intervention is discontinued.[21, 22] Here, the risk of constipation will be proactively managed with advice for high energy-free fluid intake (>2.5 litres/day) and a fibre supplement.

Participants will receive the intervention on top of the local standard care pathway that may include advice and support on pre-habilitation.

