### 9.8. Subsequent Assessments

The study schedule is available in Appendix B. The window periods will be:

- 5 days for the optional pre-operative follow-up assessment 1 (0 to 4 days post-randomisation)
- 7 days for the pre-operative follow-up assessment 2 (3 days before the time the interview is expected to occur to 3 days after that)
- 4 days for the pre-operative follow-up assessment 3 (From the day of the assessment is expected to occur (4 days pre-operatively) to the day of surgery)
- Between admission and surgery for the pre-operative follow-up assessment 4
- 27-37 days post-operative for the post-operative follow-up assessment scheduled 30 days post-operative
- 3-year follow-up from medical records: 3 years  $\pm$  9 months post-operatively

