#### Pre-operative follow -up assessment 1 – all participants (optional)

Optional QuinteT qualitative interview with all patients who consent to the main trial.

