### 14.1 xxvii. Adverse events

The information to calculate it is derived from CRF Adverse Events (any time). It is a categorical variable & each category is a count/rate (0-n/%).

| #   | Outcome Measures                                     | Control | Intervention | Delta |
|-----|------------------------------------------------------|---------|--------------|-------|
| 10b | xxvii. Adverse events (by severity)                  |         |              |       |
|     | N of AEs in category Mild                            | X       | X            | X     |
|     | N of AEs in category Moderate                        | X       | X            | X     |
|     | N of AEs in category Serious                         | X       | X            | X     |
| 10c | xxvii. Adverse events (by seriousness)               |         |              |       |
|     | N of AEs in category Serious                         | X       | X            | X     |
|     | N of AEs in category Non-serious                     | X       | X            | X     |
| 10d | xxvii. Adverse events (misc)                         |         |              |       |
|     | N of people with at least one AE                     | X       | X            | X     |
|     | N of people with at least one moderate AE            | X       | X            | X     |
|     | N of people with at least one serious AE             | X       | X            | X     |
|     | N of people with at least one SAE                    | X       | X            | X     |
|     | N of people with at least one moderate AE and/or SAE | X       | X            | X     |

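### The readable text sets no required adverse event enquiry in both arms for most of the diet period, and ascertainment differs by arm

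*Combined protocol and SAP*

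**What the plan says.** The documents give several accounts of when AEs are recorded.

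- **Protocol section 10:** "Potential AEs will be recorded at pre-operative follow-up assessment 1 and the post-operative assessment". It adds: "Participants may contact the research team (e.g., over the phone) at any time point during the course of the study to report potential AEs". Events reported between assessments go on the form for the next assessment; the example given is pre-operative assessment 2.
- **Protocol 9.8, pre-operative assessment 1:** the window is "5 days for the optional pre-operative follow-up assessment 1 (0 to 4 days post-randomisation" and the content is "Optional QuinteT qualitative interview with all patients who consent to the main trial". No AE item is listed. None is listed for assessments 2, 3 or 4 either. AEs appear only at the post-operative visit, 27 to 37 days after surgery.
- **Synopsis, AE outcome:** "xxvii: Baseline, pre-operative assessment and 30 days post-operatively". The pre-operative assessment has no number. The baseline list in 9.7 has no AE item. The primary safety outcome is timed across the whole trial.
- **Appendix B:** the AE row contains a graphic that I could not read.
- **Supplementary SAP 14.1:** AEs come from a form that can be completed at any time.

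On the window: "The safety reporting window begins from the first day of the intervention for participants in the intervention group and from the day of randomisation" for controls. It closes in both arms when the participant completes the study. The AE population (protocol 11.4, SAP 4.2, supplementary SAP 3) is all controls, but only those intervention participants who started the diet.

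Safety is progression criterion 5. The SAP bases it on related AEs and related serious AEs, adjudicated by committee without numeric limits. Supplementary SAP 14 also plans control, intervention and difference columns for AEs.

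**The concern.** The diet is the exposure whose safety is being judged. Section 9.6.1 describes its usual side effects as mostly mild, fading with time and gone once the diet stops. Events of that kind are best captured by asking during the diet or just as it ends. The only pre-operative enquiry that section 10 names is optional and comes when the diet has barely begun. The next comes a month after a major operation, when symptoms such as constipation also have to be separated from the cancer, the surgery and its complications. Complications are kept out of AE reporting altogether.

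Contact during the diet is also unequal. Intervention participants have weekly dietitian calls and pre-operative assessment 2; controls have neither. A difference in AE counts could then reflect how often people were in contact rather than harm, or real harm could go uncounted. The trial can progress only if criterion 5 is judged satisfactory, so incomplete capture matters to its main decision.

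**Working it through.** The plan states no figure for this point, so the check is calendar arithmetic and a comparison of passages.

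**Inputs.** Diet starts the day after randomisation and ends about 2 days before surgery (9.6.1). Surgery is at least 20 days after screening (8.3), with a typical 4-week window (section 5). Pre-operative assessment 1 is on day 0 to 4, assessment 3 runs from 4 days before surgery to the day of surgery, and the post-operative visit is 27 to 37 days after surgery (9.8).

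**Assumptions.** Randomisation is on the screening day and is day 0 (9.4 allows up to 24 hours). Surgery is on day W. W = 20 is the eligibility minimum, W = 28 the typical wait, and W = 35 my assumption for a delayed case.

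**Formulas.** Diet days D = W − 2. With assessment 1 on day v (0 to 4), the share of diet elapsed is v/D and the share still to come is (D − v)/D. The gap to the post-operative visit runs from W + 27 − v to W + 37 − v.

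| W | D | Elapsed at assessment 1 | Still to come | Gap to post-operative visit |
|---|---|---|---|---|
| 20 | 18 | 0/18 to 4/18 = 0–22% | 78–100% | 43–57 days |
| 28 | 26 | 0/26 to 4/26 = 0–15% | 85–100% | 51–65 days |
| 35 | 33 | 0/33 to 4/33 = 0–12% | 88–100% | 58–72 days |

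**Recall.** The last diet day is W − 2, so the post-operative enquiry comes (W + 27) − (W − 2) = 29 to (W + 37) − (W − 2) = 39 days later, whatever W is. Assessment 3 spans W − 4 to W, that is, from 2 days before the last diet day to 2 days after it.

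**Number of events.** At the 1-in-5 rate in 9.6.1, 36 × 0.2 = 7.2 intervention participants would have an attributable AE. With about seven expected, a few uncounted cases would change the picture.

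**Window start.** As planned, the arms differ by 1 day. That is 1/20 = 5.0% or 1/28 = 3.6% of the pre-operative period, and 1/50 = 2.0% or 1/58 = 1.7% of the time to day 30. This is minor.

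**Population.** Intervention participants who never start the diet drop out of the AE analysis, as do events before the first diet day in those who do; the equivalent control events stay in. The medication section foresees some participants who may not start.

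**Severity table.** Supplementary SAP table 10b grades severity as mild, moderate and then "N of AEs in category Serious". Table 10c uses the same word for regulatory seriousness, and table 10d has separate rows for a serious AE and an SAE. The first was probably meant as severe. Read literally, a severe but non-serious event has no row in 10b.

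**Expected rates.** Section 9.6.1 gives "Constipation (1 in 7), fatigue (1 in 12), headache (1 in 17), and dizziness (1 in 22"), which is 14.3%, 8.3%, 5.9% and 4.5%. Section 10 puts the same four symptoms below 8% each, so two of the four conflict. These rates enter no planned calculation.

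**The case against.** A reader might infer that AEs are collected only at two visits and that criterion 5 misses the diet. The documents do not support that. Section 10 accepts reports at any time, its window covers the whole diet, the AE form is an any-time form, and the Appendix B graphic may show continuous recording. Intervention participants also have weekly calls that check tolerance of the products, dietitian help in managing AEs (16.4), self-monitoring for those on insulin or antihypertensives, and interviews that ask about gastrointestinal symptoms. All of that stands. These contacts, however, are in one arm, and the readable text does not say that what is heard in them is entered as an AE.

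A reader might also blame the arm-specific window start for making the arms non-comparable. At one day as planned, it cannot carry that weight. Nor can it be said that most attributable events would arise between the two enquiries: the documents give no onset times and say that symptoms lessen over time.

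Finally, criterion 5 rests on related events, so it is mainly a judgement about the intervention arm, which has the most contact. Between-arm bias therefore bears chiefly on the AE secondary outcome, which is descriptive and not modelled. That also stands. Adjudication without numeric limits is a design choice and is not the defect here.

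**Conclusion.** The concern holds in a limited form. On the readable text, no active AE enquiry is required in both arms over the last 78 to 100% of an 18-day diet or 85 to 100% of a 26-day diet, and the next named enquiry is 29 to 39 days after the diet ends, with an operation in between. Diet-period events can still be reported, but only spontaneously or from late recall. The synopsis, 9.8 and section 10 do not agree on the schedule.

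Ascertainment differs by arm through the dietitian calls, pre-operative assessment 2 and the starters-only AE population. The direction of the resulting bias cannot be determined: more contact could raise intervention-arm counts, while dropping non-starters could lower them. Incomplete capture affects criterion 5; unequal ascertainment mainly affects the difference columns for the AE outcome.

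This rests on randomisation on the screening day, the planned diet dates, and Appendix B adding no required enquiry. That row should be checked first. If it shows scheduled recording in both arms, the remaining points are the inconsistency between sections and the differences in contact and population. The SAP allows for some operations less than 20 days after randomisation; those diets would be shorter than 18 days.

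**What to change.** 1. Add the existing AE list with free text (9.6.4) to pre-operative assessment 3 for all participants, and keep it at the post-operative visit. Everyone already receives assessment 3 remotely, around the end of the diet.
2. Reconcile the synopsis, 9.8, section 10 and Appendix B to that schedule.
3. Open the AE window at randomisation in both arms. Alongside the planned AE population, tabulate AEs for all randomised participants by arm.
4. Tabulate AEs by capture route, checklist or spontaneous, so that unequal contact is visible.
5. In supplementary SAP tables 10b and 10d, rename the top severity category Severe. Keep Serious for table 10c and SAE for seriousness.
6. Editorially, reconcile the expected rates in 9.6.1 and section 10.

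The cost is a protocol amendment, a slightly longer questionnaire and a few extra descriptive tables. If recruitment has closed (planned for November 2024), item 1 should go into the definitive trial's schedule. The reconciliation of the text, the all-randomised table as far as the collected data allow, the capture-route table if the route was recorded, and the label correction can still be done.

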#### **10.1. Definition of Serious Adverse Events**

A serious adverse event is any untoward medical occurrence that:

- results in death
- is life-threatening
- requires inpatient hospitalisation or prolongation of existing hospitalisation
- results in persistent or significant disability/incapacity
- consists of a congenital anomaly or birth defect.

Other 'important medical events' may also be considered a serious adverse event when, based upon appropriate medical judgement, the event may jeopardise the participant and may require medical or surgical intervention to prevent one of the outcomes listed above.

NOTE: The term "life-threatening" in the definition of "serious" refers to an event in which the participant was at risk of death at the time of the event; it does not refer to an event which hypothetically might have caused death if it were more severe.

**10.2. Reporting Procedures for Serious Adverse Events**

A serious adverse event (SAE) occurring to a participant should be reported to the REC that gave a favourable opinion of the study where in the opinion of the Chief Investigator the event was ‘related’ (resulted from administration of any of the research procedures) and ‘unexpected’ in relation to those procedures. Reports of related and unexpected SAEs should be submitted within 15 working days of the Chief Investigator becoming aware of the event, using the HRA report of serious adverse event form (see HRA website). Mortality is expected to be <4% within this setting but the Trial Steering Committee (TSC) may advise reporting to REC if the frequency of deaths is significantly higher than that expected in this population. As per 10, operative and post-operative complications that could meet the definition of SAEs will not be reported as SAEs, as they will be reported as part of the study outcomes, but the TSC will monitor the frequency of complications and may advise reporting at their discretion.

**11. STATISTICS AND ANALYSIS**

A Statistical Analysis Plan (SAP) is to be produced separately.

**11.1. Statistical Analysis Plan (SAP)**

The statistical aspects of the study are summarised here with details fully described in a SAP that will be written and finalised before the time that the first participant is recruited. The SAP will be reviewed prior to final database lock, and, if an amendment is deemed necessary, then this will be documented.

**11.2. Description of the Statistical Methods**

A table will present the baseline demographic and clinical characteristics. Continuous variables will be summarised using means, standard deviations, and 95% confidence intervals. Medians with interquartile ranges will be presented where appropriate. Categorical variables will be summarised using counts and percentages. Exploratory between-group comparisons will be reported where appropriate. Data will be analysed using appropriate statistical software.

Progression criteria (as defined in Table 2) will be summarised descriptively for all participants [and by trial group, trial site, and neoadjuvant treatment (yes/no) as appropriate]. Uncertainty in the progression criteria will be expressed with 95% confidence intervals.

Table 2: Progression criteria

| Sufficient levels of | Criterion Decision                         | Green Progress | Amber Progress with changes | Red Stop |
|----------------------|--------------------------------------------|----------------|-----------------------------|----------|
| Recruitment          | 1a Rate (n of patients per site per month) | ≥0.75          | 0.46-0.74                   | ≤0.45    |
|                      | 1b Number of sites open                    | ≥6 sites       | 3-5                         | ≤2       |

| Sufficient levels of | Criterion Decision                                                                                              | Green Progress                                                                                           | Amber Progress with changes | Red Stop |
|----------------------|-----------------------------------------------------------------------------------------------------------------|----------------------------------------------------------------------------------------------------------|-----------------------------|----------|
|                      | 1c Total N participants recruited                                                                               | 72                                                                                                       | 44-71                       | ≤43      |
| Engagement           | 2 Proportion of phone calls answered                                                                            | ≥75%                                                                                                     | 51-74%                      | ≤50%     |
| Adherence            | 3 Proportion of intervention participants with ≥5% weight loss from baseline to the day of surgery  | ≥60%                                                                                                     | 36-59%                      | ≤35%     |
| Retention            | 4 % at final follow-up                                                                                          | ≥85%                                                                                                     | 66-84%                      | ≤65%     |
| Safety               | 5 Safety profile                                                                                                | Based on adverse and serious adverse reactions. Adjudicated by the Data Monitoring and Ethics Committee. |                             |          |

 **Adherence:** Non-adherence will be defined as <2% weight loss from baseline to the day of surgery. Participants will also rate in their weekly phone call their adherence to the intervention on a 0-100 scale.

All other outcomes will be summarised descriptively by trial arm. Where appropriate, the effect size and 95% confidence intervals will be estimated with regression models adjusting for treatment group, baseline value (where applicable), and stratification variables. Both absolute and relative effect sizes will be reported. No subgroup analyses are planned.

Complications will be summarised using:

- count/percentage of participants with any complication
- count/percentage of participants with any complication by grade
- count/percentage of participants with the highest grade of complication reported
- count/percentage of participants with any type of complication
- count of total complications.

### 11.3. Sample Size Determination

With 72 patients (n=36 per arm), the trial will be 90% powered at one-sided 5% level based on the normal approximation approach to detect whether the proportions for the engagement, adherence, and retention criteria in Table 2 are truly above the upper limit of the red zone (>50% engagement, >35% adherence, >65% follow-up) based on an alternative being in the green zone.[70] The collective power for all three criteria is 85% at 5% level, without multiple testing adjustment. Recalculating the sample size on a binomial approach (sensitivity analysis) provided almost identical estimates.[70]

